### Participants (inclusion and exclusion criteria)

3.2

The sample of subjects is estimated to 130 patients, based on a 79% incidence of ALI before surgery in patients with Stanford type-A AAD^[7]^ and the set power to 80% for a type I error of 5% (Power Analysis and Sample Size, PASS V11.0, NCSS, LLC. Kaysville, UT). A convenient sample will be recruited from the Beijing Anzhen Hospital. The AAD surgery in the Beijing Anzhen Hospital is performed in approximately 300 cases per year. If 30% of these patients are eligible and consent, we will meet our recruitment target in about 1.5 years, which can avoid the bias from the different levels of surgical procedures in different periods.

Patients aged 18 to 75 years will be included. The patients with coronary heart disease; heart failure; severe cardiac tamponade; unstable hemodynamics; nervous system abnormalities; clinically apparent malperfusion^[9]^ including lower limb, cerebral, coronary, and renal malperfusion; and visceral ischemia will be excluded. All patients enrolled in this study have normal hepatic and renal function according to the preoperative physical and laboratory examinations. No patient is prescribed with nonsteroidal anti-inflammatory drugs or corticosteroids before or after admission. All patients will be informed and consented with regard to their participation in the study.

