### Definitions

3.5

In all patients, the diagnosis of AAD will be confirmed by history, chest radiography, transthoracic, and contrast-enhanced computed tomogrphy or magnetic resonance imaging. The dissection is considered as AAD if the time from the onset of the symptoms to surgery is 14 days or less. This study will only include the type-A AAD according to the Stanford classifications.^[1,2]^

The definition criteria of the ALI includes an acute hypoxemic respiratory insufficiency with bilateral pulmonary infiltrates, but is not caused by left atrial hypertension according to the left ventricular ejection fraction (LVEF). The ALI will be defined using Murray lung injury score (Murray LIS).^[12,13]^ Murray LIS consists of 4 distinct clinical parameters, including the bilateral infiltrates observed on chest radiograph, oxygenation index (PaO_2_/FiO_2_ ratio), lung compliance, and PEEP value. The severity of ALI was quantified as follows: no = the Murray LIS 0, mild to moderate = the Murray LIS 0.1 to 2.5, and acute respiratory distress syndrome = the Murray LIS > 2.5. The Murray LIS will be calculated using a specially designed tool on the web site (http://med.39.net/tools/murray.html).

Hypertension is defined as systolic blood pressure ≥140 mm Hg and/or diastolic blood pressure ≥90 mm Hg, or the need of antihypertensive agents.^[14]^ Diabetes mellitus is defined as fasting glucose level ≥126 mg/dL (7.0 mmol/L), or a glycosylated hemoglobin (Hb) ≥6.5%,^[15]^ or treatment with oral hypoglycemic agents or insulin. Smoking status will be defined as current smokers according to self-report. A glomerular filtration rate less than 60 mL/min/1.73 m^2^, and increase in serum creatinine by more than 50% times baseline is defined as impaired renal function.^[16]^

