## Statistical analysis

5

The data obtained in this study will be analyzed using SPSS 18.0 (SPSS Inc., Chicago, IL). Univariate and multiple logistic regression analyses will be used to determine the independent predictors of preoperative ALI. Univariate analysis will be applied for demographic data (age, sex, and BMI), comorbidities (smoking history, hypertension, and diabetes), preoperative data (hemodynamics, onset of symptoms to surgery, aortic diameter, LVEF, LVEDd, and EuroSCORE), surgical data (surgery time, hypothermic circulatory arrest time, intravenous colloid, crystalloid, and transfusion volumes), postoperative variables (intravenous colloid, crystalloid and transfusion volumes, urine volume, seroma volume of drainage, mechanical ventilation time, and in-hospital mortality), and serum measurements before surgery (coagulation/fibrinolysis, inflammatory, ROS, platelet, and endothelial cell function). In univariate analysis, variables associated with preoperative ALI with a *P* value <0.10 will be selected. Then, these selected variables will be put into the multiple logistic regression analysis to identify the independent predictors of preoperative ALI.

Receiver operating characteristic curve will be used to test discrimination of multivariate regression model and to determine the cutoff value in predicting preoperative ALI with sensitivity and specificity, respectively. The missing values will be displaced by means according to Intention-To-Treat rules. A *P* value <0.05 will be considered statistically significant.

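### Replacing missing values by means under an intention-to-treat label has no basis in this single cohort and biases adjusted odds ratios among correlated markers; the rule should also expressly exclude the ALI outcome

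*Protocol article*

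**What the plan says.** Section 5 (Statistical analysis) of the protocol article gives one rule for incomplete data: "The missing values will be displaced by means according to Intention-To-Treat rules". It comes after the modelling plan and the ROC plan, and it names no variables to which it does or does not apply.

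The analysis it feeds is described in the same section: "Univariate and multiple logistic regression analyses will be used to determine the independent predictors of preoperative ALI". Candidates are screened first, so that "variables associated with preoperative ALI with a *P* value <0.10 will be selected", and those selected enter the multiple model. They include continuous serum markers and binary items such as sex, hypertension and diabetes.

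Section 3.5 (Definitions) bases ALI on the Murray lung injury score (LIS), with the grades "no = the Murray LIS 0, mild to moderate = the Murray LIS 0.1 to 2.5". The same section also describes ALI clinically, as "an acute hypoxemic respiratory insufficiency with bilateral pulmonary infiltrates" that left atrial hypertension does not explain. Section 3.2 sets the sample at 130, "based on a 79% incidence of ALI before surgery in patients with Stanford type-A AAD". Both the incidence of ALI and its independent predictors are stated aims (section 2).

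**The concern.** Two things are wrong with the sentence as written.

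First, the justification does not fit. Intention-to-treat means analysing randomised participants in their assigned arm. This study has one convenience cohort and no arms. Even in a randomised trial the principle does not say how to fill a missing value.

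Second, the method damages the analysis it serves. A patient whose marker is set to the mean is no longer adjusted for that marker. Part of the marker's effect is then credited to whatever correlates with it, while its own odds ratio shrinks. The Discussion treats coagulation/fibrinolysis and inflammation as interdependent, so correlated candidates are part of the study's own premise. A mean is also not a valid value for a binary item, and it describes a skewed cytokine poorly.

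At stake is whether a marker reported as an independent predictor really is one. If the rule reached the outcome, the incidence estimate would be affected too.

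**Working it through.** The sentence carries no figure of its own to reproduce. From the document: n = 130, assumed incidence 79%, and no ALI only at LIS 0. Missing share, correlation and odds ratios are assumptions, so ranges are shown.

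**1. Covariates, n = 130.** Two standard-normal markers; one is causal (odds ratio 2.72 per SD, intercept 1.5) and the other is null. Values of the causal marker are missing completely at random and replaced by its observed mean. Both markers enter one logistic model, and the null marker is tested at 5%. There were 2,000 to 3,000 runs per setting; the ranges span repeated sets of runs.

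| Correlation | 5% missing | 10% | 20% | 30% |
|---|---|---|---|---|
| 0.7 | about 5% | 6–7% | 11–13% | about 20% |
| 0.5 | 4–5% | about 6% | about 8% | 10–12% |
| 0.3 | 5–6% | 5–6% | 5–6% | 5–6% |

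Simulation error is about one percentage point: at a rate of 6% and 2,000 runs, 1.96 × √(0.06 × 0.94 / 2,000) = 0.010. With complete data, or with complete-case analysis of the same incomplete data, the rate stays at about 4–5%. Multiple imputation that includes the outcome gave 4.0–4.3% at 20–30% missing and correlation 0.7. At correlation 0.7 and 20% missing, the null marker's median odds ratio is about 1.27 and the causal one falls from 2.72 to about 2.3. The P < 0.10 screen was not simulated. It gives no reliable protection, because a marker correlated with a causal one is itself associated with ALI before adjustment.

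**2. Is this only a small-sample effect?** No. With 20,000 patients per run, a causal odds ratio of 2.5 and incidence 79%, the odds ratios after mean substitution at 5 to 30% missing are:

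| Correlation | Null marker (true 1.00) | Causal marker (true 2.5) |
|---|---|---|
| 0.5 | 1.03 to 1.18 | 2.45 to 2.23 |
| 0.7 | 1.07 to 1.33 | 2.37 to 2.00 |

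Complete-case analysis stays at 0.99–1.00 and about 2.5.

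**3. Outcome, only if the rule were applied to the LIS.** If 79% of patients score at least 0.1, the mean score is at least 0.79 × 0.1 = 0.079. An imputed score is therefore never 0, the only value graded as no ALI. (A value between 0 and 0.1 falls in a gap of the scale, but still not under no ALI.) With true incidence p and missing share m, the reported incidence is p(1 − m) + m:

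- m = 5%: 0.79 × 0.95 + 0.05 = 0.8005, or 80.1%
- m = 10%: 0.79 × 0.90 + 0.10 = 0.811, or 81.1%

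This equals the upper extreme-case bound. The lower bound, p(1 − m), is 75.1% (0.7505) and 71.1% respectively. For scale, the 95% confidence half-width at n = 130 is 1.96 × √(0.79 × 0.21 / 130) = 7.0 points.

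**4. Room for an imputation model.** 130 × 0.21 = 27.3, so about 27 patients without ALI are expected, against more than 40 candidate variables listed across sections 4.5 and 5.

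**The case against.** A reader might infer that a patient with a missing lung score is automatically classed as ALI, and that incidence is bound to be inflated. The document does not support this. The sentence never says that the LIS is imputed, and its place after the regression and ROC plans makes predictors a natural reading. An averaged score cannot show the bilateral infiltrates in the clinical description of ALI. Section 4 also sends all ALI cases to a blinded second review. Missing scores may be rare: the physiological inputs are taken under set ventilator conditions after intubation, and chest radiography is part of the diagnosis in every patient. Even at 10% missing the shift is 2.1 points, within the 7.0-point half-width. These points stand. What remains is that no variable is exempted and that section 3.5 does define ALI through the LIS, so the text leaves the reading open.

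It can also be argued that the predictor bias is small. That is true at 10% missing or less (under about 2 points of inflation) and at correlation 0.3. The serum markers come from one sample drawn just after intubation, so 20–30% missing cannot be presumed. Even in the harsher settings most trials would not mislabel the null marker, so it would be wrong to say that false predictors will be found.

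Finally, a full chained-equations model may be unstable with about 27 non-ALI patients. That limits the remedy but does not defend mean substitution: under the same missingness, complete-case analysis keeps its nominal error rate and the prescribed rule does not.

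That an article condenses a fuller plan is no answer here, because the rule is stated, not omitted.

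**Conclusion.** The rule is wrong as written and should be fixed. The intention-to-treat label is misplaced whatever the amount of missing data. Mean substitution biases adjusted odds ratios even under the mildest missing-data mechanism. The size depends on quantities that the document does not give: negligible at 5% missing or at correlation 0.3, moderate at correlation 0.5 (up to 10–12% false positives at 30% missing), and substantial at correlation 0.7 once 20% or more is missing (11–13%, rising to about 20%). The effect on incidence is conditional on the rule being applied to the LIS, and is then 1 to 2 points upward at 5–10% missing. The document does not establish that this application is intended.

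**What to change.** - Delete the intention-to-treat wording.
- State that the Murray LIS and ALI status are not mean-imputed. Report incidence among patients with an observed status, with best- and worst-case bounds for the rest.
- For covariates, replace mean substitution with multiple imputation that includes ALI status, uses logistic models for binary items and log-transforms skewed markers. Limit the imputation model to a small set of variables, given about 27 expected non-ALI patients.
- Add complete-case analysis as a sensitivity check.

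The cost is a change of wording and a little more analysis work. No new data are needed.

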## Discussion

6

Population-based studies suggest an incidence of AAD of about 3 cases per 100,000 people per year in the United States of America.^[1]^ According to this incidence, there are almost 400,000 cases per year in China, which indicates over 20,000 patients with preoperative ALI per year. However, there has been no reliable incidence of preoperative ALI of such patients in China. Our study will be conducted in one of the largest clinic center of cardiovascular diseases in China, and a large nationally representative sample of the Standford type-A AAD in China will be collected. Therefore, the outcome of this trial can present the clinical characteristics of preoperative ALI in Chinese adult patients undergoing the Standford type-A AAD surgery.

In patients with AAD, ALI is a usual complication associated with untoward consequences or even leads to losing the chance of surgery. Although the risk factors and mechanisms of ALI are still unclear, the available evidence shows that systemic inflammatory response is activated through AAD surgery.^[4,17]^ Inflammation is a protective response essential for maintaining human health and fighting disease, but excessive inflammatory response can promote the irreversible cellular damage. The extensive activation of leckocyte and uncontrolled release of proinflammatory cytokines can increase the permeability of the vessel wall and thrombosis, which will contribute to the organs damage. Since the pulmonary vascular bed is an important reservoir of neutrophils, the lungs tend to be a major site of tissue damage by AAD.

Recent works have shown that coagulation/fibrinolysis and inflammation are host defense mechanisms, mutually dependent in mounting an adequate immune response against potentially injurious challenges.^[18]^ Furthermore, secondary fibrinolysis can aggravate ALI.^[19,20]^ Thus, we hypothesize that both the inflammation and coagulation are involved in ALI by AAD. By the statistical adjustment and analysis, it can be anticipated that findings of this study may reveal the related mechanisms of ALI by AAD. If these hypotheses are confirmed in our further clinical study, the treatments aimed to the pathophysiology of preoperative ALI can be recommended to decrease perioperative morbidity and mortality by ALI in patients with AAD. Thus, our findings have potentially clinical implications.

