### Design of trial

3.1

This trial is a prospective, double-blind, signal-center clinical trial which had been registered at www.clinicaltrials.gov (identifier NCT01894334) and approved by the Beijing Anzhen Hospital Clinical Research Ethics Committee (Fig. 1).

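### The Discussion promises a nationally representative sample, but the design supports only the proportion with ALI at anaesthesia among selected operated patients at one hospital

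*Protocol article*

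**What the plan says.** Section 6 (Discussion) notes that China has no reliable figure for how often preoperative ALI occurs in these patients, and then states that "a large nationally representative sample of the Standford type-A AAD in China will be collected". The next sentence concludes that the results can therefore describe preoperative ALI in Chinese adults having type-A dissection surgery. Section 2 (Aims) sets the same target: incidence, risk factors and mechanisms in Chinese adults undergoing that surgery.

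The design sections read differently:

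- Section 3.1: "This trial is a prospective, double-blind, signal-center clinical trial" (the third term evidently means single-centre). The Abstract says the same.
- Section 3.2, sampling: "A convenient sample will be recruited from the Beijing Anzhen Hospital".
- Section 3.2, size: "The sample of subjects is estimated to 130 patients, based on a 79% incidence of ALI before surgery".
- Section 3.2, volume and yield: "The AAD surgery in the Beijing Anzhen Hospital is performed in approximately 300 cases per year", followed by "If 30% of these patients are eligible and consent".
- Section 3.2, restrictions: age 18 to 75. Coronary disease, heart failure, severe tamponade, haemodynamic instability, neurological abnormality, clinically apparent malperfusion and visceral ischaemia are excluded. Enrolled patients have normal liver and kidney function and take no NSAIDs or corticosteroids.
- Section 4.2.5: the Murray score is obtained after anaesthesia and intubation, using the admission radiograph. Section 3.5 allows up to 14 days from symptom onset to surgery.

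**The concern.** A convenience sample from one hospital is not nationally representative, however large or prominent the hospital. This is not detail that an article leaves to a fuller document. It is a positive statement about the sample that the design sections contradict, and the Discussion rests its conclusion on it.

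The frequency of preoperative ALI is the first-named aim. If the claim stands, the percentage found in 130 selected patients will be read as the figure for operated type-A dissection in China. Two layers of selection separate the two populations. One hospital stands for the country, and within that hospital a minority of operated patients is studied after several severe presentations have been removed. Neither the aim nor the Discussion's conclusion carries these restrictions.

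A smaller matter is the label. One assessment at anaesthesia, at a varying time since onset, with no follow-up of patients initially free of ALI, gives a prevalence at that moment. The protocol calls it an incidence.

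**Working it through.** **1. The plan's own recruitment figure.** Inputs from section 3.2: 300 operations a year, 30% eligible and consenting, target 130.

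- Yearly yield: 300 × 0.30 = 90.
- Time to target: 130 / 90 = 1.44 years. The protocol says about 1.5, so this reproduces.

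The target of 130 is taken as given here. It cannot be re-derived, because the power and type I error are stated without a null value, effect size or precision. That is a separate matter and does not affect this point.

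**2. Share of the centre's operations that is studied.**

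- Operations in 1.5 years: 300 × 1.5 = 450.
- Share enrolled: 130 / 450 = 28.9%.
- Share not enrolled: about 71%.

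The 300 are described as operations for acute dissection and are not said to be type A only. The share among type-A operations could therefore be higher.

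**3. Claim against design.**

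| Property | Discussion / Aims | Design sections |
|---|---|---|
| Coverage | China | One hospital |
| Sampling | Representative | Convenience |
| Patients | Chinese adults having type-A surgery | Those also passing the section 3.2 restrictions and consenting |
| Quantity | Incidence of preoperative ALI | Proportion with ALI at one assessment after intubation |

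The first two rows contradict each other. The third is a narrowing that the conclusion does not carry. The fourth is mainly a label.

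**4. What 130 patients can deliver.** Inputs: p = 0.79 (section 3.2), n = 130.

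- Half-width: 1.96 × √(0.79 × 0.21 / 130) = 0.070, or ±7.0 points.
- Exact 95% interval for 103/130 (79.2%): 71.2% to 85.8%.

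This interval describes sampling error for the population sampled. It says nothing about how far that population differs from operated patients elsewhere, or from the patients this hospital operated on but did not enrol.

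**5. Whether consecutive enrolment is affordable.** 450 × 0.30 = 135 eligible and consenting patients in 1.5 years, against 130 needed. On these figures almost every eligible, consenting patient is needed anyway, so consecutive enrolment should take no longer. The margin is only 5 patients and depends on the 30% assumption.

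**The case against.** The best defence is that the offending words are Discussion prose. Removing them changes no eligibility rule, measurement or analysis. The restrictions are openly stated, and they are reasonable for the risk-factor and mechanism aims. Excluding heart failure also fits the case definition in section 3.5, which rules out left atrial hypertension as the cause. Incidence is often used loosely for the proportion of a surgical cohort with a complication, and sections 3.5 and 4.2.5 let a reader see what is measured. All of this stands, and it keeps the point to the claim and the target population. It does not rescue the statement about national representativeness, nor supply the missing restrictions in the aim and conclusion.

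Three stronger readings are tempting, and the document does not support them.

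- **Survivor bias in the main estimate.** Section 1 says hypoxaemia can delay surgery and so raise the risk of death, and the Discussion says that "ALI is a usual complication associated with untoward consequences or even leads to losing the chance of surgery". A reader might infer that entry to the denominator depends on the outcome and that the aim is therefore biased. But section 2 confines the aim to patients undergoing surgery, so reaching surgery defines the population. The selection matters only for the Discussion's wider phrase about type-A dissection in China.
- **A size for that bias from early mortality.** Holding section 1's 1% to 2% per hour constant gives 1 − 0.99^24 = 21.4% to 1 − 0.98^24 = 38.4% dead by 24 hours. This is all-cause mortality, not attributed to ALI, in people outside the aim. It also extends a rate that section 1 limits to the early period. At 2% per hour, 1 − 0.98^48 = 62% would be dead by 48 hours, already above the 58.0% that section 1 gives for patients not operated on.
- **A stated shift in the centre-wide figure.** If ALI frequency in the unenrolled 71% differed by 10 to 20 points, the centre-wide value would move by 0.71 × 10 = 7.1 to 0.71 × 20 = 14.2 points. The assumed difference has no support in the document, which gives neither its size nor its direction. The calculation shows only that selection could matter as much as sampling error.

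**Conclusion.** The point holds as a contradiction between the Discussion and the design. The document claims a property, national representativeness, that a single-centre convenience sample of 130 cannot have, and it draws its population conclusion from that property. What the study can report is the proportion with ALI at anaesthesia among patients meeting the section 3.2 criteria who have type-A dissection surgery at this hospital, to within about ±7 points if the proportion is near 79%. About 29% of the centre's dissection operations would be represented, on the protocol's own volume and yield.

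The contradiction itself rests on no assumption. The ±7 points assumes 79% and 130 evaluable patients. The size and direction of any selection effect are unknown. The change should be made because it concerns the first-named aim, but it does not undermine the conduct of the study.

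**What to change.** 1. In the Discussion, delete the claim that the sample is large and nationally representative, and describe it as a single-centre sample of selected operated patients.
2. Restate the first aim and the Discussion's conclusion as the proportion (prevalence) with ALI at induction of anaesthesia, with its 95% confidence interval, among patients meeting the section 3.2 criteria who undergo type-A dissection surgery at this centre.
3. In section 3.2, replace the convenience sample with consecutive eligible patients.
4. Name deaths before surgery and patients who never reach surgery as a limit on generalising to all type-A dissection, not as a bias against the stated aim.

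Items 1, 2 and 4 are text changes. Item 3 needs no longer recruitment on the protocol's figures (about 135 available, 130 needed), though the margin is thin if fewer than 30% are eligible and consent. The price is a narrower claim. No eligibility criterion, measurement or clinical procedure changes.
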